### **3.8 Justification of choice of study population**

Patients with post-infectious cough and who are older than 18, and present to GP practices will be informed about the study and invited to participate. Patients who decide to participate will be screened for eligibility. All participating subjects will sign an informed consent.

Patients who are unable to follow the study instructions or not able to give informed consent cannot participate. Female patients who are pregnant, breastfeeding or who are planning to get pregnant will be excluded from the study. Participants must also be able and willing to participate in the follow-up research interviews conducted by telephone.

## **4. STUDY OBJECTIVES**

### **4.1 Overall Objective**

The purpose of this study is to assess whether a 5-day treatment with orally administered prednisone provides patient-relevant benefits by improving the cough-related QoL of patients with post-infectious cough triggered by an URTI and seeking care in adult primary care practices. The study aims to describe an efficacy and safety profile for a 5-day prednisone treatment compared to a 5-day course of placebo.

### **4.2 Primary Objective**

To investigate whether a 5-day treatment with orally administered prednisone will be superior to placebo and improve the cough-related QoL after 14 days in patients with post-infectious cough after an URTI.

### **4.3 Secondary Objectives**

To evaluate the impact of oral prednisone on:

- Cough-related QoL at other time-points (7, 28 days and 3 months after randomization)
- Three cough-related QoL (LCQ) sub-domains, i.e. physical, psychological, and social
- Overall cessation of cough, i.e. proportion of patients without cough symptoms 7, 14, and 28 days after randomization

### **4.4 Safety Objectives**

To evaluate the impact of oral prednisone on:

- Safety outcomes, i.e. re-consultations at GP and/or hospitalisations
- Total AE within 3 months after randomization
- SAE within 3 months after randomization.

To assess any potential harms, we will evaluate any AE and specifically SAE according to the WHO-UMC causality categories “certain”, “probable”, “possible”, and “unlikely” (16).

## 5. STUDY OUTCOMES

### 5.1 Primary Outcome

The primary outcome is *cough-related QoL assessed by the LCQ score 14 days after randomisation*.

To assess the impact of the treatment and control medication on patients' QoL, the LCQ will be used. The LCQ takes 5 to 10 minutes to complete (10). The LCQ has already been used in a similar randomised-controlled trial assessing the effectiveness of montelukast in the treatment of post-infectious cough (15). The LCQ is a validated QoL measurement tool for non-specific cough, developed for self-administration and assesses the impact of cough on various aspects of life, including emotions, sleeping behaviour, work and relationships. It contains 19 items which are divided over 3 domains: physical (8 items), psychological (7 items) and social (4 items); with a 7-point Likert scale (11). The LCQ is short, easy to administer, suitable for capturing longitudinal developments in cough and cough-related wellbeing, and can be useful in clinical trials assessing new medications for cough (11). We will use the validated German version of the original LCQ (13), which is kindly provided by [name]. [name], Head of Pneumology, Department of Medicine, University of Freiburg im Breisgau, [name], Germany.

### 5.2 Secondary Outcomes

- Cough-related QoL assessed by the LCQ score 7, 28 days and 3 months after randomisation.
- Cough-related QoL sub-domains physical, psychological, and social 7, 14, 28 days and 3 months after randomisation.
- Overall cessation of cough 7, 14, 28 days and 3 months after randomisation.
- Incidence rate of re-consultations at GP and/or hospitalisations within 3 months following randomisation.

### 5.3 Other Outcomes of Interest

None.

### 5.4 Safety Outcomes

- Incidence rate of re-consultations at GP and/or hospitalisations within 3 months following randomisation
- Total AE within 3 months after randomization
- SAE within 3 months after randomization
- Changes in glucose levels for patients with pre-study controlled diabetes that are deemed by GP to exceed the hypothesized benefit on cough.

## 6. STUDY DESIGN

### 6.1 General study design and justification of design

OSPIC is a 1:1 randomised, parallel-group, placebo-controlled, superiority trial with blinded patients, physicians and outcome assessors in a primary health care setting.

Recruitment will take place in GP practices in the Northwestern, Central Switzerland and the Canton of St. Gallen. These GPs will recruit 5 to 10 patients over an 18-months period to reach the target sample size (N=204).

To ensure that the study is conducted in accordance with GCP-guidelines, GPs will receive study-specific training prior to study start. In addition, GPs will be provided with a tailored GCP training specific for the responsibilities they assume for this study, including training on providing patient information and consenting and on detection, documentation and reporting of adverse events. The training consists of a video and written transcript of the key points presented in the video. The video training material was developed by the *Institut für Hausarztmedizin Bern* together with CTU Bern based on CTUs GCP course material. This GCP training was accepted by the *Kantonale Ethikkommission des Kantons Bern* for two recently submitted clinical trials: Optimizing Pharmacotherapy In the Multimorbid Elderly in Primary Care: the OPTICA Trial and the Efficacy of Metamizole versus Ibuprofen and a Short Educational Intervention versus Standard Care for patient with Acute and Subacute Low Back Pain: A Randomized, Factorial Trial. EMISI Studie (PI Prof. [name], Bern) The video can be accessed at <https://video.aum.unibe.ch/BIHAM-Videos/>, under the name file *Instruktionsvideo für Hausärzteinnen\_v111018.mp4*. A transcript of the instruction video is attached to the section 17. Appendices. GPs will have to confirm that they watched the video and read the training material before they start recruiting patients. A platform like ILIAS (or similar) will be used to deliver the training and submit the confirmation.

Patients with post-infectious cough presenting in practices will be given full written and verbal explanations of the trial purpose, potential benefits and risks, and then will be invited to participate. Patients who agree to join the study will be screened against the full eligibility criteria. Participants will have sufficient time to ask questions and it will be stated clearly that non-participation does not influence the standard of care in any way. Formal written consent will be taken from those agreeing to participate.

Once patients are informed about the OSPIC trial (by their GP) and written informed consent is obtained (day 0), they will be randomly allocated to prednisone or placebo treatment. We select a dose of 40mg (2 tablets of 20 mg) of prednisone once daily over 5 days because of pharmacokinetic evidence suggesting that a minimum dose of 20 mg prednisone daily is required for non-asthmatic patients to achieve an adequate anti-inflammatory effect (26) and because the first trial of its kind should use an adequate and sufficient dose to detect any potential effects, as concluded in a systematic review by El-Gohary et al. (5): “adequately powered research is warranted, in primary care, to further clarify the benefits and harms of corticosteroids for adults with acute and post-infectious cough. Because it is not clear from this review where the dose-response threshold lies, it would appear sensible to test the effects of high-dose (e.g. 40 mg prednisone daily) oral steroids first. If no effect is seen, it would seem unlikely that even high dose inhaled steroids would be effective”. We select a treatment duration of 5 days since post-infectious cough is thought to be mediated by inflammatory processes comparable to those in exacerbations of asthma or COPD. For these conditions there is strong evidence that short-term oral corticosteroids for 5 days provide patient-relevant benefit without relevant harm (9).

After informed consent is obtained, GPs will provide participants with the pre-randomized study medication. Oral and written instructions on how the medication should be taken will be provided to the study participants. In the event of a missed dose, patients are instructed to continue medication intake on the next day. Participants who complete the study are required to return empty medication glass jars to their GPs as soon as this convenient for them (e.g. on the occasion of the next consultation). Participants will be asked by the research staff/ study nurse about their medication intake at the first phone call on day 7.

The expected duration of participant's participation is around 3 months. The participation includes day 0 (enrolment, information on the study, informed consent, allocation to study group, completion of the LCQ with their GP, administration of study drugs), the treatment period of 5 days, and the follow-up phone call by the research staff/study nurse on days 7, 14, 28 and at 3 months after randomization. The telephone calls for the study follow-up are expected to last around 15 minutes each. In case phone calls are not answered, follow-up phone calls will be performed several times and participants will be sent reminder emails. If the participant is not reached for the follow-up call at day 7, then a call will be made in the next 2

days (days 7 +2). When participants are not reached for the follow-up calls at days 14 and 28, they will be called again on the next two days (day 14 +2; days 28 +2). If participants are not reached by telephone at 3 months, they will be called by the research staff during the next 7 days (3 months +7 days).

To include 204 participants the recruitment period will last 18 months and cover two winter seasons when the incidence of URTIs is very high and post-infectious cough is very common. The length of the recruitment period was especially defined to include more than one winter season, to ensure successful recruitment and even though coughing is prevalent throughout the year and patients can be affected in summer as well.

All GPs, clinical investigators and research staff/study nurses involved in the study as well as all patients will remain blinded with respect to the randomisation throughout the trial. The study medication is labelled, packed and dispensed by the University Hospital Basel Pharmacy according to the randomisation procedure. If safety concerns require to know the patient's allocated intervention, the GP can request an unblinding provided by the CTU using the secuTrial®. Each unblinding is documented in the EDC's integrated audit trail system.

At baseline visit, patients will be randomly assigned in a 1:1 ratio either to the active treatment or the control group. Patients are considered being smokers, when answering to the baseline questions that they had smoked "more than 100 cigarettes in their life", that they smoke "daily" or "sometimes" (29).

## **6.2 Methods of minimising bias**

### **6.2.1 Randomisation**

At baseline visit, patients will be randomly assigned in a 1:1 ratio either to the active treatment or the control group. Pre-randomised, identically looking, numbered and marked medication glass jars with 5 daily doses of 40 mg (2 tablets of 20 mg) of prednisone (intervention group) or placebo (control group) are provided by GPs to participants. The randomisation procedure will be implemented by the CTU of the University Hospital Basel. The CTU Basel will generate a randomisation list with a 1:1 treatment allocation. This list will be the basis for labelling and packing of the study medication in cooperation with the University Hospital Basel Pharmacy. The study medication will be directed to the GPs who will hand participants the pre-randomized medication glass jars in the order of reception of the medication glass jars. Following this procedure, participants will therefore be randomly allocated to either prednisone or placebo medication. With the randomisation list being only accessible by the CTU Basel and the University Hospital Basel Pharmacy, the treatment allocation is concealed from patients, physicians and other involved personnel.

### **6.2.2 Blinding procedures**

All GPs, clinical investigators and research staff/study nurses involved in the study as well as all patients will remain blinded with respect to the randomisation throughout the trial. The study medication is labelled, and packed and dispensed by the University Hospital Basel Pharmacy according to the randomisation list provided by the CTU Basel. Participants in the study will receive a medication guide stating that they are taking either placebo or prednisone tablets (40 mg) daily for a period of 5 days as part of the OSPIC study. In case participants require hospitalizations or they consult a different doctor (not their GP), they are encouraged to take the medication guide with them. GPs will not have access to the randomization list and in case of urgency they have to request the unblinding by making a request with the OSPIC study team.

### **6.2.3 Other methods of minimising bias**

None.

## **6.3 Unblinding Procedures (Code break)**

If safety concerns require to know the patient's allocated intervention, the GP can request an unblinding by making a request with the OSPIC study team who will inform the CTU as soon as possible (during

working hours). After receiving the unblinding request the CTU can break the code by using the secuTrial®. Each unblinding is documented in the EDC's integrated audit trail system.

## 7. STUDY POPULATION

The aim is to enrol a total of 204 patients with post-infectious cough within a period of 18 months. Patients will be recruited by participating GPs running a general practice in North-western and Central Switzerland. The geographical area is large enough to recruit the required number of patients in the indicated timeframe as nearly 40% of adults can be affected by post-infectious cough after an acute respiratory infection (15, 28). Patient recruitment in primary practices in the German speaking part of Switzerland will continue until the sample size is reached. It is envisaged that the recruitment period will last about 18 months: First-patient-in in February 2020 and last-patient-out in July 2021. We expect that most participants will be enrolled during the two winter seasons when the incidence of URTIs is very high and post-infectious cough is very common. The length of the recruitment period was specifically defined to include more than one winter season, to ensure successful recruitment and even though coughing is prevalent throughout the year and patients can be affected in summer as well. In case of unforeseen difficulties with patient recruitment and lack of a reasonable number of participants after 9 months (e.g. less than 1/3 of target study population enrolled), the recruitment areas can be enlarged since the investigators have established cooperation with institutes of “Hausarztmedizin” in the Eastern part of Switzerland and in the French speaking part of Switzerland. Additionally, the number of randomised patients per GP (limited to 10) can be increased. If the enrolment goals are not met, the study will be submitted to other regional ethics committees in order to expand this study geographically.

### 7.1 Eligibility criteria

Participants fulfilling all of the following inclusion criteria are eligible for the study:

- Age ≥ 18 years
- Seeing a GP for a dry or productive post-infectious cough (3 to 8 weeks) after an URTI
- Able and willing to give informed consent by themselves

The presence of any one of the following exclusion criteria will lead to exclusion of the participant:

- Patients with hypersensitivity to prednisone or to one of the adjuvants in the drug's composition
- Patients with known or suspected diagnoses associated with cough, such as: pneumonia, allergic rhinitis, sinusitis, bronchial asthma, chronic pulmonary disease (COPD), gastroesophageal reflux disease
- Patients with other chronic disease such as bronchiectasis, cystic fibrosis, cancer, tuberculosis, heart failure
- Use of inhaled or oral corticosteroids within the last four weeks
- Immunodeficiency/immunocompromised state (e.g. cancer chemotherapy, HIV infection)
- Pregnancy/breastfeeding, as evaluated through screening
- Regular treatment known to be associated with cough (e.g. angiotensin-converting enzyme inhibitors)
- Patients with a documented diagnosis of glaucoma or osteoporosis in the GP's patient health record
- Experienced fractures due to osteoporosis
- Patients with uncontrolled diabetes (as deemed by GPs who appraise whether the potential side effects of short-time corticosteroids on glucose levels exceed the hypothesised benefit on cough)

It is at the discretion of the treating GP to physically examine the patient. GPs will screen all female participants of reproductive age (postmenarche to menopause) using a battery of questions and will exclude all females who are pregnant, plan or are actively trying to get pregnant or women who are potentially pregnant. Women potentially pregnant are defined as those women who respond that they are not using safe contraception or that they think they are pregnant or that they may be pregnant. Safe contraception is considered to be the use of the following contraception methods: oral contraceptive drugs, birth control implant such as Implanon NXT®, intrauterine device or coil such as Mirena®, every 3-months contraceptive injection e.g. Depo-Provera 150® or always using condoms during intercourse.

Women with anamnestic risk of pregnancy shall not be included in this study (unprotected sexual intercourse in the last two weeks). Pregnancy testing (laboratory or at-home tests) is not required for this study. Please see section 10.1.2 for additional information on handling risk of pregnancy for this study. The GP may perform different tests if necessary (i.e. laboratory test, pulmonary function test). Also, GPs will appraise whether the potential side effects of short-time corticosteroids on glucose levels exceed the hypothesized benefit on cough, particularly in diabetic patients.

## **7.2 Recruitment and screening**

Family practice will be identified through existing research networks by the Centre for Primary Health Care, University of Basel, and the Institute of Primary and Community Care, University of Lucerne, through personal contact, and by mail. In total 472 GPs of this network in North-western and Central Switzerland have already been approached by an online survey in November 2016. Of these, 183 GPs replied (39%). A case vignette (32-year old, healthy non-smoker without asthma, who has had dry cough for 4 weeks) was presented to them and they were asked about their management of post-infectious cough, namely if they would prescribe topical or oral steroids and whether they would take part in a trial assessing the treatment of post-infectious cough. Results were presented at the SSGIM (Swiss Society of General Internal Medicine) congress in Lausanne in May 2017. Overall, 52% (n=94) of GPs indicated to agree to participate in an intervention study assessing the efficacy of corticosteroids in patients with post-infectious cough (30).

Patient recruitment will take place in primary care practices in the German speaking part of Switzerland and will continue until the sample size is reached. Study leaflets and posters will be distributed to collaborating GPs to advertise the study in their family practices. To ensure uniform questioning during the trial (LCQ) and to minimise differences, GPs and research staff/study nurses will receive a trial specific training by CTU and study team members. In case of any queries, [name]. med. [name] or the study nurse can be contacted at any time via phone or email. It is envisaged that the recruitment period will last about 18 months: First-patient-in in February 2020 and last-patient-out in July 2021. We expect that most participants will be enrolled during the two winter seasons. However, clinical experience indicates numerous cases of post-infectious cough also during warmer periods of the year (31).

Patients with post-infectious cough presenting in practices will be given full written and verbal explanations of the trial purpose, potential benefits and risks. They will have sufficient time to ask questions and it will be stated clearly that non-participation does not influence the standard of care in any way. Patients who agree to participate will be screened for eligibility. Formal written consent will be taken from those agreeing to participate. The paper CRF will be completed by the GP and the medication glass jars containing prednisone or placebo will be handed to the participant. The number of randomised patients per GP is limited to 10. In case of recruitment problems (scheduled numbers of study participants not reached at predefined milestones) this limit can be increased.

Patients will not receive any financial compensation for study participation as the burden for them is minimal and they do not have any additional expenses for travelling, medical devices or other items. GPs will get a refund of 100 CHF per recruited patient to cover their fixed costs. The 100 CHF value for compensation is based on a review of financial data from basic providers in the canton Zürich published in "Schweizerische Ärztezeitung" in 2004 (32).

## **7.3 Assignment to study groups**

At baseline visit, patients will be randomly assigned in a 1:1 ratio either to the active treatment or the control group. The randomisation procedure will be implemented by the CTU of the University Hospital Basel and a randomization list will be generated (see also section 6.2.1). This list will be provided to the University Hospital Basel Pharmacy for the purpose of labelling and packaging the medication. The medication packages will be delivered to GPs who will distribute the medication in the order of reception and therefore randomly allocate recruited participants to either the treatment or the control medication.

## **7.4 Criteria for withdrawal / discontinuation of participants**

Due to the short intervention of 5 days, no treatment modifications are planned unless in the (unlikely) occasion of AE (e.g. allergic reactions to the study drug, psychotic, or pre-psychotic episode) or occurrence

of SAE (e.g. sepsis, venous thromboembolism, and fracture) (27) or other urgent reasons (pregnancy, cancer diagnosis, infection other than URTI). In any of those cases the treatment will be stopped immediately. Treatment will also be discontinued when study participants withdraw their informed consent. Study participants are given the possibility to withdraw from the OSPIC trial without justification at every stage and at any time.

In the follow-up phone calls participants will be asked about concurrent medication, including if they started a treatment with antibiotics. In the case that participants are prescribed and start the antibiotics treatment during the study's 5-days medication, then those participants will be discontinued from the study.

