## 8.5 Data Collection and Follow-up for withdrawn participants

Participants in the study will be asked at each follow-up call at day 7, 14, 28 and after 3 months from enrolment whether they are still happy to participate in the study. Participants who wish to withdraw have the possibility to either (1) inform their GP who then records this in the participant file; (2) inform the study team directly by phone or mail; (3) inform the research staff at one of the follow-up phone calls. Participants who have withdrawn from the study will not be followed-up if they do not wish to be contacted. Data collected until the time of withdrawal will be used for the intention to treat analysis.

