## 8.6 Trial specific preventive measures

Any co-treatment or co-medication (i.e. antitussives, inhalation, herbal teas, and homeopathic pharmaceuticals) is permitted except for the use of corticosteroids. The use of any other medical intervention by study participants will be recorded in electronic Case Report Forms (eCRF) to analyse potential influence on outcomes.

GPs will screen all female participants of reproductive age (postmenarche to menopause) using a battery of questions and will exclude all females who are pregnant, plan or are actively trying to get pregnant or women who are potentially pregnant. GPs will advise participants that they need to use contraceptives for the duration of the study and that they should inform the GP or the study team in case they suspect they have become pregnant. Women with anamnestic risk of a pregnancy shall be excluded from this study. If a participant gets pregnant during follow-up, course and outcome of the pregnancy should be followed up carefully by GPs, documented and reported. Please see section 10.1.2 for additional information on handling risk of pregnancy for this study.

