#### **9.2.5 Assessments in participants who prematurely stop the study**

GPs will inform the patient on the importance to adhere to the 5-day medication intake in a manner consistent with usual care recommendations to follow the treatment as prescribed. The GPs will remind participants on the importance for the trial conduct to be available for the follow-up phone calls. Participants are encouraged to answer the follow-up questions. If patients prematurely stop the study or do not answer the follow-up call, the study team can contact the GP to ask about possible GP visits (AEs or SAEs) or hospitalizations (i.e. for pneumonia). Data will be collected until the time of withdrawal and will be analysed in the intention to treat analysis.

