#### 11.4.2 Primary Analysis

Analysis of the primary objective will follow the intention-to-treat (ITT) principle. It will be based on the full analysis set (FAS). FAS will include all patients who gave informed consent. Patient data will be analysed according to their treatment allocation.

We will test if there is a difference of the LCQ score between the intervention and control group 14 days after randomization. A treatment effect of 1.3 points increase will be considered as MCID.

The hypothesis will be tested using analysis of covariance (ANCOVA). We will report the treatment effect with 95% confidence intervals (CI). Covariates of the ANCOVA model will be baseline LCQ scores, duration of cough, age, sex, and smoking status. Patients are considered as smokers, when they answer that they had smoked “more than 100 cigarettes in their life”, they smoke “daily” or “sometimes” to the participant survey (29).

Baseline characteristics of patients in the FAS will be presented stratified by group and summarized in a table.

To assess the robustness of our primary analysis, the following sensitivity analyses will be performed:

- Analysis of the primary outcome without imputing data (complete case analysis)
- Analysis of the primary outcome using the per-protocol data set (PPS) which is defined above
- Exploring interactions between covariates of the ANCOVA model of the primary analysis
- Exploring how the effect of the intervention varies among GP practices. For this, a linear mixed-model with treatment group as a fixed-effect and GP practices as a random effect will be fit.

We will conduct one subgroup analysis, comparing effects on the primary outcome in current smokers vs. current non-smokers. Subgroup effects will be analyzed by interaction tests and interpreted fully exploratory. We expect that effects are more pronounced in non-smokers according to reports by Ponsioen et al. (20).

Statistical analysis will be performed by the CTU of the University Hospital Basel using R language and environment ([www.r-project.org](http://www.r-project.org)).

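### Section 7.4 takes participants who start antibiotics during the five medication days out of the study, not only off the tablets, so their day-14 primary outcome would probably go uncollected

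*Protocol*

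**What the plan says.** The primary outcome (Protocol 5.1) is "cough-related QoL assessed by the LCQ score 14 days after randomisation". On the analysis, 11.4.2 states: "Analysis of the primary objective will follow the intention-to-treat (ITT) principle". Section 11.4.1 puts every randomised patient in the full analysis set (FAS).

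Section 7.4 has two rules with different wording:

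- For adverse events, serious adverse events, pregnancy, a cancer diagnosis or an infection other than URTI: "In any of those cases the treatment will be stopped immediately".
- For antibiotics started during the five medication days: "then those participants will be discontinued from the study".

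The route by which the study team learns of antibiotic use is also in 7.4: "In the follow-up phone calls participants will be asked about concurrent medication, including if they started a treatment with antibiotics". The first of these calls is on day 7 (+2 days).

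On data after leaving the study, 9.2.5 says: "Data will be collected until the time of withdrawal and will be analysed in the intention to treat analysis". Section 8.5 says: "Participants who have withdrawn from the study will not be followed-up if they do not wish to be contacted".

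On other treatment, 8.6 says that any co-treatment or co-medication "is permitted except for the use of corticosteroids". A parenthesis in that sentence names antitussives, inhalation, herbal teas and homeopathic products. Section 8.3 leaves additional treatment to the GP and cross-refers to 7.4.

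**The concern.** Starting an antibiotic happens after randomisation, and it plausibly reflects worsening or a suspected infection. Its frequency could differ between arms in either direction. Prednisone might relieve symptoms and so reduce prescribing, yet section 3.7 lists a raised infection risk among the documented effects of short courses.

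If such an event ends participation before day 14, the primary outcome is missing for a reason probably related to prognosis and possibly related to treatment. An intention-to-treat analysis needs the outcome from everyone randomised, and the calls that would supply it are already scheduled. The day-28 and 3-month calls, which also collect adverse events, would be lost in patients with a possible infection. For these patients 9.2.5 only says that the team can contact the GP.

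**Working it through.** **1. The passages side by side.**

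- Section 7.4 distinguishes stopping treatment from leaving the study, and gives antibiotic starters the second. An infection other than URTI stops only the tablets, while an antibiotic given for that infection ends study participation.
- When antibiotic use comes to light at the day-7 call, the tablet days are normally over. What remains is the day-14, day-28 and 3-month follow-up. If the GP prescribes the antibiotic, it may be known earlier, and the rule can then act during the tablet days.
- Section 9.2.5 collects data until withdrawal. Section 8.5 ends contact for those who do not want it and does not mention participants removed by the protocol. No passage says that antibiotic starters are still called at day 14.

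**2. What the analysis can do about it.** Section 11.5 imputes by chained equations if data are missing (completely) at random, and promises sensitivity analyses otherwise. A starter found at the day-7 call can still give a day-7 LCQ in that call, so baseline and day-7 scores may be available. If the removal rule is followed, no starter has an observed day-14 score, and the imputation model must extrapolate from patients who did not start antibiotics.

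**3. Reproducing the sample size.** Inputs from 11.2: difference 1.3, SD 3.3, two-sided alpha 5%, power 80%.

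n per arm = 2 × (1.960 + 0.842)² × 3.3² / 1.3² = 101.2, rounded up to 102, so N = 204 as stated. The t-test solution is 102.1 per arm. N has no explicit drop-out inflation.

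**4. Power.** Exact two-sample t-test, difference 1.3, SD 3.3. The 10% drop-out is from 11.2. The further 3-8% antibiotic loss, and its adding to the 10%, are assumptions.

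| Patients with day-14 LCQ | Derivation | Power |
|---|---|---|
| 204 | all randomised | 80.0% |
| 184 | 204 × 0.90 | 75.7% |
| 178 | 184 × 0.97 | 74.3% |
| 169 | 184 × 0.92 | 72.1% |

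The rule itself costs 75.7 − 74.3 = 1.4 to 75.7 − 72.1 = 3.6 percentage points. Ordinary drop-out accounts for 4.3.

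**5. Bias of a complete-case contrast.** Let pT and pC be the shares lost on prednisone and placebo, and D the amount by which the lost patients' mean day-14 LCQ lies below that of the retained patients, equal in both arms. Then bias = (pT − pC) × D. All values are assumptions.

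| pT | pC | D = 2 | D = 3.3 | D = 5 |
|---|---|---|---|---|
| 5% | 5% | 0 | 0 | 0 |
| 2% | 6% | −0.08 | −0.13 | −0.20 |
| 2% | 10% | −0.16 | −0.26 | −0.40 |
| 6% | 2% | +0.08 | +0.13 | +0.20 |
| 10% | 2% | +0.16 | +0.26 | +0.40 |

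Against the MCID of 1.3, 0.08 is 6% and 0.40 is 31%.

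**The case against.** A reader might infer that the rule breaks the intention-to-treat analysis. It does not. Antibiotic starters stay in the FAS and are analysed as allocated, the data they gave before leaving are used, and 11.5 provides imputation or sensitivity analyses. The defect is missing data that could have been avoided.

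A reader might also infer that the protocol expressly deletes the day-14 outcome. That is the natural reading of 7.4 with 9.2.5, but it is not stated: 9.2.5 does not say that antibiotic starters count as withdrawn, and 8.5 ends contact only for those who do not want it. This leaves the matter open and does not secure the day-14 call.

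The figures are open to challenge, and the challenge stands. The bias applies to a complete-case contrast, which 11.4.2 uses only as a sensitivity analysis. The primary analysis is a baseline-adjusted ANCOVA with missing data handled under 11.5, and its residual bias has not been calculated. That antibiotic starters do worse is a plausible inference without data in the protocol. Only starts within five days count, so the number may be small. Section 11.2 also relies on a conservative SD and an ignored baseline correlation to absorb drop-out.

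The conflict with 8.6 is a tension, because the parenthesis there does not name antibiotics and 7.4 is the more specific rule. The wording still needs aligning.

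**Conclusion.** The point holds as a correctable weakness. As written, the plan most naturally stops collecting the primary outcome, and later safety data, after a post-randomisation event that is plausibly related to prognosis, and no other section clearly prevents this. Intention-to-treat is weakened, and imputation under missing at random would rest on extrapolation.

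Neither size nor direction can be fixed from the protocol, which gives no antibiotic rate and no outcome for this group. With assumed losses of 2% in one arm and 6-10% in the other, and a deficit of 2-5 points, a complete-case contrast shifts by about 0.1-0.4 LCQ points. It does not shift if loss and deficit are equal across arms. With an assumed 3-8% loss beyond 10% drop-out, power falls from about 76% to 72-74%. Most of the fall from 80% to 74% comes from the drop-out; at the upper end of the assumed loss the two contributions are closer. The case for change rests mainly on its low cost and on the fact that a day-14 score not collected cannot be recovered later.

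**What to change.** - In 7.4, state separately what ends study medication and what ends data collection.
- State that a participant who starts an antibiotic stays in all scheduled follow-up calls unless consent is withdrawn, that the antibiotic is recorded, and that the day-14 LCQ is analysed in the FAS by allocated arm.
- Align 8.3, 8.5, 8.6 and 9.2.5 with this. In 8.5, distinguish participants who withdraw from those whose study medication is ended by the protocol.
- If antibiotic starters are to be left out of the per-protocol set, amend 11.4.1, which at present defines that set by tablet adherence and complete LCQ scores.

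Whether the study tablets are stopped when an antibiotic is started is a clinical decision for the sponsor and is not addressed here.

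The cost is limited rewording across these sections. The calls are already scheduled and concomitant treatments are already recorded at each of them. The only added work is completing calls that would otherwise be dropped.
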